# Prevention of hepatic encephalopathy by administration of rifaximin and lactulose in patients with liver cirrhosis undergoing placement of a transjugular intrahepatic portosystemic shunt (TIPS): a multicentre randomised, double blind, placebo controlled trial (PEARL trial)

**DOI:** 10.1136/bmjgast-2020-000531

**Published:** 2020-12-28

**Keywords:** hepatic encephalopathy, liver cirrhosis, portal hypertension

## Abstract

**Introduction:**

Cirrhotic patients with portal hypertension can suffer from variceal bleeding or refractory ascites and can benefit from a transjugular intrahepatic portosystemic shunt (TIPS). Post-TIPS hepatic encephalopathy (HE) is a common (20%–54%) and often severe complication. A prophylactic strategy is lacking.

**Methods and analysis:**

The Prevention of hepatic Encephalopathy by Administration of Rifaximin and Lactulose in patients with liver cirrhosis undergoing placement of a TIPS (PEARL) trial, is a multicentre randomised, double blind, placebo controlled trial. Patients undergoing covered TIPS placement are prescribed either rifaximin 550 mg two times per day and lactulose 25 mL two times per day (starting dose) or placebo 550 mg two times per day and lactulose 25 mL two times per day from 72 hours before and until 3 months after TIPS placement. Primary endpoint is the development of overt HE (OHE) within 3 months (according to West Haven criteria). Secondary endpoints include 90-day mortality; development of a second episode of OHE; time to development of episode(s) of OHE; development of minimal HE; molecular changes in peripheral and portal blood samples; quality of life and cost-effectiveness. The total sample size is 238 patients and recruitment period is 3 years in six hospitals in the Netherlands and one in Belgium.

**Ethics and dissemination:**

This study protocol was approved in the Netherlands by the Medical Research Ethics Committee of the Academic Medical Centre, Amsterdam (2018-332), in Belgium by the Ethics Committee Research UZ/KU Leuven (S62577) and competent authorities. This study will be conducted in accordance with Good Clinical Practice guidelines and the principles of the Declaration of Helsinki. Study results will be submitted for publication in a peer-reviewed journal.

**Trial registration numbers:**

ClinicalTrials.gov (NCT04073290) and EudraCT database (2018-004323-37).

## Introduction

### Portal hypertension and TIPS

Liver cirrhosis is the most common cause of portal hypertension (PH). Complications of PH include (refractory) ascites and oesophageal or gastric variceal bleedings. These complications are severe and result in hospital admissions and decreased survival. Moreover, cirrhotic patients undergo physical deterioration due to undernutrition and muscle wasting and are physically frail.^1^

A transjugular intrahepatic portosystemic shunt (TIPS) reduces PH, by decompression of the portal system through an artificial shunt from a intrahepatic portal vein to a hepatic vein. TIPS can be considered as therapy for refractory ascites and variceal bleeding. TIPS treatment for refractory ascites has a response rate, defined as improvement of ascites, of up to 85%.^2 3^ A meta-analysis showed improved survival of cirrhotic patients receiving a (uncovered) TIPS, with a decreased risk of refractory ascites and hepatorenal syndrome.^4^ However, these patients have an increased risk of hepatic encephalopathy (HE). Improvement of survival was confirmed in a recent randomised controlled trial (RCT): 1-year transplant-free survival was significantly higher in patients who received TIPS (93%) compared with patients who were treated with large volume paracentesis (LVP) and albumin infusion (52%) and suggested that TIPS should be the first line of treatment of refractory ascites.^5^

Another consequence of PH is the development of gastric or oesophageal varices. One-third of the patients who are diagnosed with liver cirrhosis and are compensated have oesophageal varices, and in patients presenting with ascites, this is the case in up to 60%.^6^ Seventy per cent of all upper gastrointestinal bleeding episodes in patients with cirrhosis are caused by variceal bleeding.^6^ In patients with multiple bleeds, high risk of treatment failure (recurrence of variceal bleed), or increased mortality risk (Child Pugh C (<11 points) liver cirrhosis), a TIPS is a highly effective intervention (94%) to control bleeding.^7^ Hence, TIPS is a very effective intervention to treat complications of PH.^2 3 7^ However, also these patients are at risk for post-TIPS HE.^8–10^

### Hepatic encephalopathy

HE is a common complication in patients with liver cirrhosis and is associated with profound loss of quality of life. HE is a brain dysfunction caused by liver insufficiency and/or portosystemic shunting; it manifests as a wide spectrum of neurological or psychiatric abnormalities ranging from subclinical alterations to coma.^11^ HE is classified using the West-Haven criteria: minimal HE (MHE), covert HE (grade I) or overt HE (OHE, grades II–IV).^12^ MHE is subtle cognitive impairment that is difficult to detect clinically and only by psychometric testing. The psychometric hepatic encephalopathy score (PHES) and simplified one min animal naming test (S-ANT1) are two validated instruments to measure MHE.^13 14^ PHES exists of a line tracing test, digit symbol test, serial dotting test and a number connection test.^13^ S-ANT1 is a 1 min test in which patients name as many animals as possible. The outcome of this test was validated to score MHE.^14^ OHE presents with a varying severity and symptoms as disorientation, motor dysfunctions, abnormalities in behaviour, intellectual functions and consciousness. Thirty to forty-five per cent of patients with liver cirrhosis develop OHE during the course of their disease.^15^ HE leads to a prolonged duration of hospital admissions, an increased number of primary care contacts, an impaired quality of life and increased mortality.^11 16–19^

### Treatment and prevention of OHE

The initial treatment of OHE is non-absorbable disaccharides like lactulose.^11^ The dosing of lactulose should be initiated with 25 mL of lactulose every 12 hours and the dose should be titrated to achieve two soft or loose bowel movements per day.^11^ The working mechanism of lactulose is not fully understood, but it is assumed that the prebiotic effects and acidifying nature of lactulose have an additional benefit beyond the laxative effect.^20 21^

There is currently no treatment registered for primary prevention of HE. Secondary prevention of HE can be achieved by combination therapy of lactulose with rifaximin, a poorly absorbed antibiotic. In the Netherlands, rifaximin has been approved since 2016 and will be reimbursed only to prevent a third (or following) episode of OHE.^22^

### Post-TIPS HE

HE is a common and often severe complication after TIPS placement. Incidence of new onset OHE or worsening of MHE after TIPS is approximately 20%–54%.^7–10^ Risk factors for post-TIPS HE are mainly described for uncovered stents in retrospective studies. Extensive prospective evidence is lacking and little evidence is available for covered stents. Prior HE episodes, increased CP score and increased age are possible risk factors, but there is no consensus about the exact limits.^23^ In patients with variceal bleeding, a TIPS diameter of 8 mm can decrease the incidence of post-TIPS HE compared with 10 mm.^24^

The International Club of Ascites published their sixth position paper on PH in 2015.^25^ Both this group of international experts in PH as well as the European Association for the Study of the Liver (EASL)/American Association for the Study of Liver Diseases (AASLD) practice guidelines have prioritised studies on treatment and prevention of (post-TIPS) HE on the research agenda because of the lack of strong evidence regarding primary prevention.^11 25^ Besides a missing strategy to prevent HE after TIPS placement, it is currently not possible to predict whether patients will suffer from post-TIPS HE. Moreover, possible biomarkers currently are lacking.

### Prevention of post-TIPS HE

An RCT, Riggio *et al*, showed that rifaximin (1200 mg/day) alone or lactitol (60 mL/day) alone did not prevent HE after TIPS placement.^26^ It is unclear whether polytetrafluoroethylene covered stents or bare metal stents were used. Although not fully published yet, a more recent RCT, Bureau 2019, does show a positive effect of rifaximin on post-TIPS HE. In this trial, rifaximin 1200 mg/day was started 15 days before TIPS placement until 6 months post-TIPS.

The combination of rifaximin and lactulose has never been tested to prevent post-TIPS HE. This might prove to be a more effective strategy, as it has been shown to be effective in the prevention of recurrent HE and is current standard of care.^27^ In this particular RCT—both in patients with and without TIPS—a reduction of 58% in episodes of HE was realised, and a 50% reduction in the risk of hospitalisation was achieved.^27^ Two other double-blind RCTs confirmed that combination of lactulose and rifaximin decreased the risk of HE.^28 29^ Apart from inhibition of intestinal bacterial RNA synthesis, effects of rifaximin on intestinal cells can be observed within 24 hours. Intestinal barrier function is improved, and there is an upregulation of enzymes involved in detoxification.^30 31^ Based on the effectiveness of lactulose and rifaximin, we hypothesise that the combination of lactulose and rifaximin will reduce the number of patients with post-TIPS HE.

## Objectives

### Primary objective

To assess the incidence of post-TIPS OHE within the first 3 months after prophylactic administration of lactulose and rifaximin versus lactulose and placebo in patients who undergo covered TIPS placement.

### Secondary objectives

To assess:

Ninety-day mortality.Transplant-free survival.The development of a second episode of OHE within the first 3 months after covered TIPS placement.The development of OHE between 3 and 12 months after covered TIPS placement.Time to development OHE or MHE episode(s).The change in PHES and S-ANT1 test during the study: at time points week 4, week 12 and week 52, compared with baseline.The change in Liver Frailty Index score at week 12 and week 52, compared with baseline.Differences in molecular composition of peripheral/portal blood samples at TIPS placement.Differences in molecular composition of peripheral blood samples at baseline, compared with day 10 post-TIPS, week 4, week 12 and week 52.Quality of life.Costs and cost-effectiveness.

## Methods and analysis

### Trial design

The Prevention of hepatic Encephalopathy by Administration of Rifaximin and Lactulose in patients with liver cirrhosis undergoing placement of a TIPS (PEARL) trial, is a multicentre randomised, double blind, placebo controlled trial. Six academic hospitals from the Netherlands and one academic hospital from Belgium will be involved in the recruitment. In order to minimise burden for the study subjects, this trial has been designed in such a way that visits for patients are the same as standard of care. A flowchart of the trial design is found in figure 1.

**Figure 1 F1:**
[figure not shown]
Flowchart of the Prevention of hepatic Encephalopathy by Administration of Rifaximin and Lactulose in patients with liver cirrhosis undergoing placement of a TIPS (PEARL) trial.

### Eligibility criteria

#### Inclusion criteria

All of the following criteria must be met in order to be eligible for participation in this trial:

Elective-covered TIPS placement for refractory ascites (a) and/or recurrent variceal bleeding (b):Recurrent tense ascites and at least one of the following criteria:Not responding to the maximal dose of diuretics (400 mg spironolactone and 160 mg furosemide).Kidney insufficiency (creatinine >135 μmol/L) induced by diuretics.Electrolyte disturbances (sodium <125 mmol/L, potassium >5.5 mmol/L) induced by diuretics.Not tolerating higher dose of diuretics (eg, because of subjective side effects like muscle cramps).(Recurrent) variceal bleeding, not responsive to treatment with endoscopic band ligation and/or beta-blockers, with a high risk of failure of endoscopic treatment:Patients with a variceal bleeding and Child-Pugh C (10–13 points) cirrhosis orPatients with a variceal bleeding, Child-Pugh B and an active bleeding during endoscopy.Age ≥18 years.Confirmed liver cirrhosis as documented by liver biopsy, elastography (eg, Fibroscan) or combination of usual radiological and biochemical criteria.Signed informed consent.

#### Exclusion criteria

Any absolute contraindications for TIPS placement:History of HE grades II–IV without precipitating factor (such as dehydration, variceal bleeding, SBP or other infection).Heart failure New York Heart Association ≥grade 3.Hepatocellular carcinoma (multifocal or large or centrally located).Systemic infection/sepsis.Severe pulmonary hypertension.Unrelieved bile duct obstruction.Technically not feasible.Poor liver function (Model for End-stage Liver Disease (MELD) score >20).Use of ciclosporin (124-fold higher systemic exposure rifaximin).^32^Life-threatening variceal bleeding with emergency TIPS placement that cannot be delayed for 72 hours.Age >80 years.Non-cirrhotic PH.Portal vein thrombosis (main trunk).HIV.Current or recent (<3 months) use of rifaximin.Overt neurologic diseases such as Alzheimer’s disease, Parkinson’s disease.Pregnant or breastfeeding women.

### Randomisation and concealment of allocation

After the screening visit, eligible study subjects will be stratified for MELD score <10 and >10. Study subjects are stratified randomised to the treatment or placebo in a 1:1 ratio. Randomisation with random blocks of sizes 4, 6 or 8 is performed by Castor Electronic Data Capture (Ciwit B.V., The Netherlands) in an automated way and sent to the local clinical trial pharmacy. Neither the treating physician nor the patient is aware of the randomisation result. Deblinding is possible in the case standard of care that might be withheld (see safety paragraph).

### Intervention

Rifaximin 550 mg two times per day will be prescribed, in combination with a starting dose of 25 mL lactulose two times per day and further dependent on the amount of daily bowel movements, with the objective of two soft stools per day. In the case of a study subject already being treated with lactulose, that dose will be used. Intervention will start 72 hours before TIPS placement and will last till 3 months after TIPS placement. The control group will receive placebo in combination with lactulose (as described above).

In the event of lactulose-related diarrhoea, dosage will be lowered to 10 mL two times a day. If diarrhoea persists: dosage is lowered to 5 mL two times a day. Once subjects have no diarrhoea anymore, dosage can be increased, with the objective to achieve two soft stools a day.

### Outcome measures and study procedures

#### Primary outcome

The development of OHE within 3 months after covered TIPS placement is determined by the West Haven criteria.

#### Secondary outcomes

Ninety-day mortality; development of a second episode of OHE within the first 3 months; development of OHE in the period between 3 and 12 months after covered TIPS placement; development of MHE between covered TIPS placement and 12 months after placement; time to development of OHE or MHE episodes; increase in the PHES, S-ANT1 score and LFI compared with baseline. Difference in the composition of portal blood samples, drawn at TIPS placement. TIPS placement data will be recorded. Furthermore, quality of life will be assessed by the Liver Disease Symptom Index V.2.0 (LDSI V.2.0) and EQ-5D-5L questionnaires. Costs will include costs of healthcare, productivity loss due to sick leave from work and out-of-pocket expenses.

### Assessment schedule

A detailed assessment schedule is found in table 1.

**Table 1 T1:** Time and events schedule—PEARL trial

Procedure	Screening	Day 7 (baseline)	Day 3	Day 0 TIPS	Day 10	W4	W12	W26	W52
**Window (days**)	max - 21	±4			±7	±7	±7	±7	±7
**Eligibility assessments**									
Informed consent	X								
Inclusion/exclusion criteria	X								
Medical history +concomitant medication	X								
**Study medication**									
**Assessments**									
**Physical examination***	X	X			X	X	X	X	X
Liver frailty index		X					X		X
Assessment of hepatic encephalopathy by West Haven criteria	X	X			X	X	X	X	X
Assessment of hepatic encephalopathy by PHES and S-ANT1		X				X	X		X
**Assessment of quality of life†**		X					X		X
**Economic evaluation questionnaires‡**		X					X		X
Assessment of adverse events				X	X	X	X	X	X
Assessment of compliance and concomitant medication				X	X	X	X	X	X
**Laboratory tests**§	X	X			X	X	X		X
Storage of peripheral blood and/or portal (*) vein blood		X		X*			X		X
Storage of stool sample		X		X			X		X
Storage of saliva samples		X		X			X		X
Radiological assessment and flow measurement	X				X		X		X

NB: Visit day 7 might be the same as the day of start study medication.

*Height and weight, vital signs, including pulse rate, blood pressure, respiration rate and temperature, signs of ascites or oedema.

†EQ-5D-5L questionnaire and LDSI 2.0 questionnaire.

‡Adapted version of the Productivity Cost Questionnaire and Medical Consumption Questionnaire.

§Clinical chemistry: sodium, potassium, serum creatinine, glucose, alanine aminotransferase, aspartate aminotransferase, total and direct bilirubin, alkaline phosphatase, gamma-GT, C reactive protein, albumin, ammonia. Coagulation: international normalised ratio, PT. haematology: haematocrit, haemoglobin.

PHES, Psychometric Hepatic Encephalopathy Score; S-ANT1, simplified one min animal naming test.

### HE assessment

HE will be assessed by West Haven criteria during all study visits. Additionally, HE is assessed by PHES and S-ANT1 at baseline, week 4, week 12 and week 52.

### Frailty assessment

Liver Frailty Index test will be performed at baseline, week 12 and week 52.

### TIPS placement data

The following data of TIPS placement will be recorded: intravenous antibiotic prophylaxis, method of anaesthesia, per procedural medication, mean ventilation pressure, TIPS placement technique, length of puncture canal, type of covered stent (Viatorr or Viatorr Controlled Expansion), length, diameter and dilatation of this stent, duration of the procedure, visualised collaterals, pressure measurements, embolisation and registration of possible complication(s).

### Quality of life and economic evaluation questionnaires

Quality of life questionnaires are evaluated by EQ-5D-5L and LDSI V.2.0 at baseline, week 12 and week 52. Economic evaluation questionnaires to assess healthcare used and productivity losses are handed out as well at these time points.

### Peripheral and portal blood samples

As shown in table 1, peripheral and portal blood samples will be taken from study subjects at several time points. Patients will be requested to fast 12 hours before blood withdrawal in order to avoid interference with, for example, dietary components in the analysis. Samples of peripheral blood at baseline will be compared with the samples at week 12 and week 52. Samples of peripheral blood (4 hours - 5 min before TIPS placement) will be compared with portal blood samples. Portal samples will be withdrawn directly after TIPS placement using a catheter. When there are clinical signs that a reintervention of the TIPS is inevitable, additional portal and peripheral blood samples will be withdrawn. Additional sampling of portal blood can only occur with a maximum of three times during the first 3 months. In the case that reintervention is necessary after 3 months, another two additional times of sampling are possible in the study period between 3 and 12 months after TIPS placement.

Untargeted metabolomics will be used to study differences in peripheral and portal blood samples as well to study differences in peripheral blood samples from the different time points. Moreover, lipidomics and small molecule analyses will be performed, all using liquid chromatography with tandem mass spectrometry. A more targeted approach is dependent on the results of these experiments.

### Saliva and stool samples

For two ancillary studies, saliva and stool samples are collected for microbiome analyses in some participating centres (due to logistical reasons and a smaller sample size) at baseline, day 0, week 12 and week 52.

### Statistical considerations

#### Sample size

The incidence of post-TIPS OHE is 20%–54% in international studies.^7–10^ To determine the incidence of new onset or worsening HE in our own population, we performed a retrospective analysis of the last 16 years of patients undergoing TIPS placement.^33^ This study revealed that approximately 33% of the patients suffered from new or worsening of existing HE within 30 days after TIPS placement. Between 30 and 90 days after TIPS placement, 17% still had HE. Actual percentages might be higher due to the retrospective nature of the study. Reduction of HE is achieved in 58% of the patients.^27^ However, due to selection bias, we estimate that in our study population. 50% reduction is realistic. The calculation of the sample size (nQuery Advisor V.7.0) was done for a χ^2^ test. Assuming that the effect of rifaximin and lactulose is a 50% reduction of HE, incidence of HE is expected to drop from 33% to 16.5%. With a two-sided 5% alpha, power of 80%, a total of 107 study subjects are needed in both groups. With an estimated dropout of 10%, a total of 119 study subjects are needed in the intervention group and 119 study subjects in the control group.

### Analysis of outcome measures

A comprehensive statistical analysis plan (SAP) will be provided separately. Data will be analysed according to the intention to treat principle. Descriptive methods will be used to assess quality of data, homogeneity of treatment groups and endpoints. A p value <0.05 is considered statistically significant. A brief outline is given in the next paragraph.

#### Primary outcome measurement

The primary outcome, development of OHE within 3 months after TIPS placement determined by the West Haven criteria, will be compared between the intervention and placebo group. Percentage differences with corresponding 95% CI will be reported as absolute improvement in percentages.

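### Randomisation is stratified by MELD, but the outlined primary comparison does not use the stratum; if MELD predicts overt HE, a crude interval is slightly too wide and a crude test slightly conservative

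*Protocol article*

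**What the plan says.** **Design.** Under Randomisation and concealment of allocation, "eligible study subjects will be stratified for MELD score <10 and >10". The next sentence adds: "Study subjects are stratified randomised to the treatment or placebo in a 1:1 ratio". Random blocks of 4, 6 or 8 are used.

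**Sizing.** Under Sample size, "The calculation of the sample size (nQuery Advisor V.7.0) was done for a" chi-square test. OHE is assumed to fall from 33% to 16.5%. No strata are mentioned.

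**Primary analysis.** Under Primary outcome measurement, OHE within 3 months "will be compared between the intervention and placebo group. Percentage differences with corresponding 95% CI will be reported" as an absolute improvement. No test, stratum or covariate is named.

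**Other analyses.** Under Secondary outcomes in the analysis section, the methods named are the t-test, Mann-Whitney U, chi-square, Kaplan-Meier curves, Cox models, a signed rank test and mixed models. None is described as stratified by MELD.

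**Status of the text.** Analysis of outcome measures calls this a brief outline and says that a full SAP will be provided separately.

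**The concern.** Blocked randomisation within strata forces the arms to be nearly balanced on MELD. The part of the outcome variance that lies between strata then no longer adds to the sampling variance of the risk difference. A crude standard error still counts it. If OHE risk differs between the strata, the crude interval is wider than the design warrants and the crude test rejects too rarely under the null. The point estimate hardly moves, because 1:1 allocation within strata makes the crude and stratified differences almost equal.

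What is at stake is a little precision on the primary endpoint. There is also a practical matter: if the choice between crude and stratified results is not fixed before unblinding, it stays open when a p value falls near 0.05.

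**Working it through.** **Inputs from the article.** Control risk 0.33, intervention risk 0.165, two-sided alpha 0.05, power 80%, 107 per arm, 119 per arm after 10% dropout, two MELD strata, 1:1 allocation.

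**Assumed, because the article gives no figure.** The share *s* of patients in the low-MELD stratum (20%, 30%, 50%) and the gap *g* in control OHE risk between strata (0, 10, 20, 30 points). The control average is held at 33% and risk is halved by treatment in each stratum.

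**1. The plan's own figure.** With pooled variance under the null and no continuity correction:

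n = [1.96 × √(2 × 0.2475 × 0.7525) + 0.8416 × √(0.33 × 0.67 + 0.165 × 0.835)]² / 0.165²
= (1.1962 + 0.5042)² / 0.027225 = 106.2, so 107 per arm.

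Then 107 / 0.90 = 118.9, so 119 per arm. Both stated figures reproduce; 107 per arm gives 80.3% power.

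**2. Crude interval.** Per-patient variance sum = 0.2211 + 0.1378 = 0.3589. Half-width = 1.96 × √(0.3589 / 107) = 11.35 points.

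**3. Stratified interval.** The between-stratum variance is s(1 − s)g² in the control arm and s(1 − s)(g/2)² in the intervention arm. Subtract both. For s = 0.5 and g = 0.20 (23% vs 43%):
- between-stratum part = 0.0100 + 0.0025 = 0.0125
- variance ratio = (0.3589 − 0.0125) / 0.3589 = 0.965
- half-width = 11.35 × √0.965 = 11.15 points

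Since s(1 − s) peaks at s = 0.5, a larger low-MELD share cannot make any given gap worse than this.

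**4. True alpha of the crude test.** Under the null both arms have control risks, so the ratio is (0.4422 − 0.0200) / 0.4422 = 0.955. Alpha = 2 × [1 − Φ(1.96 / √0.955)] = 0.045.

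**5. Power.** The true standard error is the stratified one in both cases; only the critical value differs. For the same case, 107 per arm:
- crude: Φ[(0.165 − 0.1156) / 0.0569] = 80.7%
- stratified: Φ[(0.165 − 0.1139) / 0.0569] = 81.6%

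**6. Range over s = 20 to 50%.**

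| Gap (points) | Stratified half-width (crude: 11.35) | Crude CI too wide by | True alpha, crude | Power, crude | Power, stratified |
|---|---|---|---|---|---|
| 0 | 11.35 | 0 | 0.050 | 80.3% | 80.3% |
| 10 | 11.30–11.32 | 0.3–0.4% | 0.049 | 80.4% | 80.5–80.6% |
| 20 | 11.15–11.22 | 1.1–1.8% | 0.045–0.047 | 80.6–80.7% | 81.1–81.6% |
| 30 | 10.90–11.06 | 2.6–4.2% | 0.039–0.043 | 80.9–81.3% | 82.1–83.1% |

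**7. Simulation check.** There were 200,000 trials per scenario, 107 per arm, balanced within strata. With s = 30%, null rejection for chi-square against CMH was 0.046 against 0.049 at 20 points, and 0.041 against 0.050 at 30 points. Power was 81.3% against 81.8%, and 81.8% against 83.1%. At zero gap both tests rejected at 0.051 under the null, and power was 81.1% for chi-square against 80.8% for CMH. Stratifying on a non-prognostic factor therefore costs about 0.3 points at most here.

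**The case against.** The strongest reply is that the article does not commit to a crude analysis. The primary outcome paragraph never says unadjusted; a Mantel-Haenszel difference would fit its wording. The chi-square test is named for sizing and for categorical secondary outcomes, and sizing on an unstratified test is common practice. The text is declared an outline, with detail left to an SAP that is not shown. This stands, so the point is conditional and cannot be called an established error. What remains is that a stratified design is fixed in one section and every analysis section is written without it.

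Three stronger readings are tempting, and the article supports none of them.

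- *The confidence interval is wrong.* A reader might infer this from stratified randomisation alone. It needs MELD to be prognostic, and no OHE risk by MELD stratum is given. The article states that "Prior HE episodes, increased CP score and increased age are possible risk factors"; MELD is not in that list, and no reason for stratifying on it is given. Patients with MELD above 20 are excluded, which narrows the range.
- *The trial loses its planned power.* The 107 per arm was computed for the unstratified test, which keeps 80.3 to 81.3% analytic power in every scenario above. Stratifying adds a margin; it does not repair a deficit.
- *Age and prior HE ought to be in the model.* They are named only as possible risk factors and are not used in the randomisation. Adjusting for them is optional and forms no part of this point.

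**Conclusion.** The point holds in a limited form and is of low priority. As outlined, the primary comparison does not use the stratum by which patients are randomised. If the analysis is in fact crude, and if MELD predicts OHE, the interval is slightly too wide and the test slightly conservative. For a moderate assumed gap of 10 to 20 points the interval is off by less than a quarter of a percentage point in half-width (11.35 against 11.15 at most), with the alpha and power effects shown in the table. The 30-point rows mark an extreme. With equal risks in the strata the effect is nil. In no scenario does ignoring the stratum inflate type I error or undermine the 107 and 119 per arm.

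The direction follows from the design. The size rests wholly on assumed stratum shares and risks.

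**What to change.** State in the SAP, before unblinding, that the primary analysis is the Mantel-Haenszel risk difference stratified by MELD with its 95% CI, tested by the CMH test, and keep the crude difference and chi-square test as supportive. Use the stratum recorded at randomisation; the article's two categories do not say where a score of exactly 10 belongs, so the SAP should define this. Carry the same stratum into the Cox models.

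The cost is wording only: the stratum is already recorded for every randomised patient, and the sample size does not change. If the separate SAP already specifies a MELD-stratified primary analysis and Cox models, nothing further is needed.
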